#### Subgroup analysis

Subgroup analysis will be as follows: 1) preoperative NRS2002 scoring (< 3 group and ≥ 3 group); and 2) pathological TNM staging (stage I, stage II, and stage III) to precisely analyze the advantage of uncut Roux-en-Y anastomosis.

## Discussion

In recent years, gastric cancer has remained the fourth most common malignant disease worldwide, and lower one-third gastric cancer is the most common type [1–3]. Distal gastrectomy with D2 lymph node dissection has been thought to be the standard surgery for these patients [4]. However, reconstruction of distal gastrectomy remains controversial; Billroth II anastomosis has gained widespread popularity for its simplicity and lower risk of anastomotic tension. In addition, Billroth II anastomosis may cause bile reflux gastritis, esophagitis, or dumping syndrome [13]. Therefore, the preferred way to perform reconstruction after distal gastrectomy is still debated. Uncut Roux-en-Y anastomosis is another method of reconstruction with an anti-reflux function as well as the ability to eliminate the occurrence of Roux stasis [20, 21]. However, it requires further investigation to have an impact in clinical practice.

Many investigators have evaluated the anastomosis after distal gastrectomy by randomized controlled trials [19, 26–29]. However, most of these studies were conducted with a small population at a single center. Moreover, there are no prospective studies to confirm the definite superiority of uncut Roux-en-Y anastomosis for patients after distal gastrectomy. Therefore, we propose a multicenter, prospective, randomized clinical trial primarily to elucidate the safety of uncut Roux-en-Y anastomosis compared to Billroth II anastomosis and to innovatively evaluate patients’ nutritional status and quality of life. The SPIRIT 2013 checklist provided the recommended items to address in a clinical trial protocol (shown in Additional file 2).

Moreover, we plan to do some subgroup analysis using the different preoperative nutrition status or the postoperative pathological stages as analysis factors. In our trial, region supervisors will monitor the researchers with regard to completeness of data collection. However, it is unavoidable to have some missing data. As we mentioned in the “Elimination criteria” section, patients whose efficacy evaluation data for the treatment are incomplete will be excluded. Other missing data are divided into two kinds—important data and common data—depending on the relationship of the missing data and the primary or secondary assessment of the trial. We will record and report the number of cases where the randomized treatment cannot be performed. We will try to fix the common data using statistical tools. However, if the missing data are important, we will employ a specialist of statistics to analyze and decide how to deal with them.

However, bias exists in all clinical trials. In our trial, the blinding of the surgeons and patients as to the intervention is the most challenging aspect of designing a randomized controlled trial involving surgical procedures. For others, the blinding of patients should also be considered to reduce potential bias. Therefore, we set purely objective variables as the primary endpoints, including endoscopy and laboratory tests. Additionally, multicenter trials are associated with biases, including differences in operative skill. We have tried to eliminate these biases by examining the surgical procedure by another hospital and training all surgeons at participating centers in standard procedures.

To conclude, based on previous efforts in the reconstruction of distal gastrectomy, the proposed CSGC002 trial represents a multi-center, prospective, randomized controlled trial to test the hypothesis that uncut Roux-en-Y anastomosis can reduce postoperative complications and improve the nutritional status of gastric cancer patients after D2 gastrectomy compared to Billroth II anastomosis. We believe that the results of the trial will significantly contribute to the evidence on which to base the reconstruction of distal gastrectomy.

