### Randomization

After completing an initial assessment and signing an informed consent form, participants will be randomized into two groups: the experimental group undergoing uncut Roux-en-Y anastomosis and the control group undergoing Billroth II anastomosis.

The randomization is undertaken only by the qualified researchers. A secure randomization routine will give each patient an identification number. This number must be recorded in the randomized list together with the randomized data. The completed list should be signed by the investigators and submitted to the data center along with the patients’ initial information. Patients’ identification numbers should be marked in all the relevant reports.

During the randomization, allocation concealment should be maintained. All the patients will be randomized into groups in a 1:1 ratio, and neither surgeons nor patients will be informed as to the randomization arm before surgery. Once D2 gastrectomy has been performed, the randomization arm of the patient will be revealed and the corresponding anastomosis will be performed.

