### Uniformity in surgical performance

Assuring uniformity in surgical performance is the key point for our multi-center clinical trial. Therefore, the surgeons definitely should be trained and the operative procedures monitored. It is worth mentioning that the surgeons should at least have clinical experience in conducting radical gastrectomy for more than 3 years or more than 100 cases.

Before the trial, the leading center will appoint qualified surgeons to train the other surgeons in the coordinating centers. It is relatively easy for them to master the new technique for the reason that the uncut Roux-en-Y anastomosis is based on Billroth II anastomosis with the addition of the side-to-side anastomosis between the jejunum approximately 35 cm from gastrojejunostomy and the jejunum approximately 5 cm from the ligament of Treitz and closure of the intestinal cavity on the input less than 5 cm from the loop gastrojejunostomy anastomosis using uncut closure devices.

In particular, it is required to take pictures of the surgery field including the lymph node dissection area and the anastomosis field in order to make sure that the performance is qualified. These pictures will be uploaded to the database and checked by the data managers. If the operation does not achieve the standard of either D2 gastrectomy or corresponding anastomosis, the case will be rejected.

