### Outcome measures

All patients enrolled in this trial will be followed up regularly at stated intervals after the surgery for an average of 5 years. During the follow-up visits, patients will undergo endoscopy, laboratory tests, and radiography if necessary as described in Table 1.

**Table 1 Tab1:** Summary of the follow-up visit schedule and assessed parameters at each time point

	Preoperative	3 M	6 M	9 M	12 M	18 M	24 M	36 M	48 M	60 M
Endoscopy	*	**	*		*		*	*	*	*
Laboratory	*	*	*		*		*	*	*	*
CT scan	*	*	*		*		*	*	*	*
Upper digestive tract radiography	**	*	*		*		*	*	*	*

*Evaluation at the designated time point, **evaluation if necessary

The primary assessment indices of the study are reflux gastritis, esophagitis, bile regurgitation, and anastomotic ulcer. Endoscopy will be used to help with standardized assessment of these indices during the follow-up visits. Full details for the Los Angeles classification of the severity of reflux esophagitis are shown in Table 2.

**Table 2 Tab2:** Los Angeles classification of the severity of reflux esophagitis

Grade	Manifestation
A	One (or more) mucosal break(s) no longer than 5 mm that does not extend between the tops of two mucosal folds
B	One (or more) mucosal break(s) more than 5 mm long that does not extend between the tops of two mucosal folds
C	One (or more) mucosal break(s) that is continuous between the tops of two or more mucosal folds but which involve(s) less than 75% of the circumference
D	One (or more) mucosal break(s) that involve(s) at least 75% of the esophageal circumference

The secondary assessment indices are nutritional status, quality of life, perioperative complications, overall survival rate, and others. Nutritional status includes body mass index (BMI), hemoglobin, albumin, total protein, pre-albumin, transferring, and other indices such as appetite and Onodera’s prognosis nutritional index (PNI). Quality of life will be assessed by the gastrointestinal symptom rating scale (GSRS) and Visick score (shown in Additional file 1: Tables S1 and S2). Perioperative complications occurring within 30 days after the surgery include anastomotic fistula and anastomotic stenosis. Overall survival rates for 1, 3, and 5 years after the surgery as well as recurrence and metastasis rates will be calculated. Other indices include surgery time, intraoperative blood loss, length of hospital stay, and hospital cost.

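### The Discussion answers the blinding problem with 'purely objective' primary endpoints, but the outcome that sizes the trial is a visual endoscopic judgement with no stated scale or assessor masking, and laboratory tests are not primary endpoints

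*Protocol article*

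**What the plan says.** In the bias paragraph of its Discussion, the protocol article says that "the blinding of the surgeons and patients as to the intervention is the most challenging aspect of designing a randomized controlled trial" for surgical procedures. After a remark that blinding of patients should be considered, it concludes: "Therefore, we set purely objective variables as the primary endpoints, including endoscopy and laboratory tests". The other measures in that paragraph, surgeon training and a check of the procedure by another hospital, deal with operative skill and not with how outcomes are read.

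Under Outcome measures: "The primary assessment indices of the study are reflux gastritis, esophagitis, bile regurgitation, and anastomotic ulcer". The method is endoscopy: "Endoscopy will be used to help with standardized assessment of these indices during the follow-up visits". The one scale shown is for esophagitis: "Full details for the Los Angeles classification of the severity of reflux esophagitis are shown in Table 2". Haemoglobin, albumin and the other laboratory values appear there under nutritional status, a secondary outcome. The Sample size section names reflux gastritis (present or absent) as the primary outcome and expects 8% with uncut Roux-en-Y and 12% with Billroth II.

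Concealment is described under Randomization. Before the operation, "neither surgeons nor patients will be informed as to the randomization arm before surgery". After the gastrectomy, "the randomization arm of the patient will be revealed and the corresponding anastomosis will be performed".

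**The concern.** Objectivity is the only protection that the article offers the primary endpoint against knowledge of the arm. For reflux gastritis and bile regurgitation it is not a property of the measurement. Someone looks at the remnant mucosa and decides whether gastritis is present, or whether the bile seen counts.

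Any expectation has a known direction. The Background and Discussion say that Billroth II may cause bile reflux gastritis and that uncut Roux-en-Y has an anti-reflux function. A reader who knows the arm and shares that view errs toward the trial's hypothesis. The planned difference is only 4 points, so a small error that differs by arm would matter.

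The sentence also conflicts with the plan in a way that needs no assumption about masking. It counts laboratory tests among the primary endpoints, whereas Outcome measures makes them secondary.

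**Working it through.** **Inputs from the Sample size section:** 8% v 12%, 80% power, 5% level, 15% drop-out, 416 per group. Evaluable after drop-out: 416 × 0.85 = 353.6, taken as 353. The analysis is Pearson's χ² or Fisher's exact test (Statistical analysis).

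**The plan's own figure.** The 416 does not reproduce. For 12% v 8%, the pooled two-proportion formula gives 882 per group two-sided (1038 after drop-out) or 695 one-sided (818 after drop-out). That is a separate matter. It enters here only because it sets the number of patients for the calculation below.

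**Assumed scenario.** The true rate is 8% in both arms. A share f of unaffected Billroth II patients is wrongly called positive, and none is in the uncut Roux-en-Y arm. The documents give no value for f, so a range is shown.

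Observed Billroth II rate = 0.08 + 0.92 × f. The full planned 12% is reached at f = 0.04 / 0.92 = 0.0435, about 1 in 23. That is 0.04 × 353.6 ≈ 14 extra calls, or 0.04 × 416 ≈ 17.

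**Chance of a false significant result favouring uncut Roux-en-Y** (two-sided 5%, normal approximation): Φ[(d − 1.96 × SE0) / SE1], where d is the observed difference, SE0 = √(2 × p̄ × (1 − p̄) / n), and SE1 = √((p1(1 − p1) + p2(1 − p2)) / n).

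Example with n = 353, p1 = 0.12, p2 = 0.08:
- SE0 = √(0.18 / 353) = 0.02258
- SE1 = √(0.1792 / 353) = 0.02253
- (0.04 − 1.96 × 0.02258) / 0.02253 = −0.19, so Φ = 0.425

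| f | Observed Billroth II | False difference (points) | n = 353 per arm | n = 416 per arm |
|---|---|---|---|---|
| 0 | 8.0% | 0 | 2.5% | 2.5% |
| 1% | 8.9% | 0.9 | 6.4% | 6.9% |
| 2% | 9.8% | 1.8 | 13.5% | 15.2% |
| 3% | 10.8% | 2.8 | 24.1% | 27.6% |
| 4.35% | 12.0% | 4.0 | 42.5% | 48.5% |

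With 882 per arm, the last row would be 80%.

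**Over-calling must differ by arm.** With a true 8% in both arms, equal over-calling leaves no difference. With a true 12% v 8%, equal over-calling of 4.35% shrinks the difference to 0.04 × (1 − 0.0435) = 0.038.

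**The text side by side.** Randomization covers surgeons and patients, before surgery only. The photographs required under Uniformity in surgical performance are of the operative field, not of follow-up endoscopy. No section shown says who reads the endoscopies or what they are told.

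**The case against.** The strongest reply is that this is a condensed article. The full protocol, Figures 2 and 3 and the additional files are not shown, and they could name masked endoscopists or a gastritis scale. That stands. A reader might infer that the endoscopists know the arm, but the documents do not say so. Randomization says only that the arm is revealed so that the anastomosis can be done. Nor does the Discussion plainly give up on blinding, since it says that patient blinding should be considered. The supportable statement is that the article states no assessor masking and shows no scale for gastritis or bile. Neither a scale nor masking elsewhere would make a visual call purely objective, or make laboratory tests primary.

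Outcome measures does call the endoscopic assessment standardized. That favours consistent reading, but it does not remove a reader's expectation.

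The second reply is that 4.35% is solved backwards from the planned effect and needs all the error in one arm. That also stands. It is an illustration, not an estimate. The calculation is per patient, because the article does not say how the six scheduled readings from 6 to 60 months combine.

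**Conclusion.** The safeguard stated in the Discussion does not hold for reflux gastritis, the outcome that sizes the trial, or for bile regurgitation. Its mention of laboratory tests contradicts Outcome measures. Both conclusions rest on the text alone.

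The size rests on assumptions: a true 8% in both arms, error confined to Billroth II, and 353 to 416 evaluable patients per arm. Over-calling of 1%, 2% and 4.35% then raises the chance of a false positive result for uncut Roux-en-Y from 2.5% to about 6–7%, 14–15% and 43–49%.

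A reader might go further and conclude that the planned effect would be an artefact. The documents do not support that. They give no misclassification rate, and even the 4.35% scenario reaches significance less than half the time at the planned size. Esophagitis graded by Los Angeles and anastomotic ulcer are less exposed, and the point does not depend on them.

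**What to change.** Under Outcome measures, for all remaining follow-up endoscopies:
- The request form for the study reading does not name the arm. 'Distal gastrectomy with gastrojejunostomy' is true of both, since "the uncut Roux-en-Y anastomosis is based on Billroth II anastomosis with the addition of the side-to-side anastomosis between the jejunum" and a closure of the input limb.
- The endoscopist comes from existing staff and is not on the operating team.
- Gastritis and bile in the remnant are graded on a pre-specified scale, and esophagitis by Los Angeles.
- These findings and anastomotic ulcer are recorded, with photographs, before the scope passes the gastrojejunostomy. The operative record stays available afterwards.

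In the Discussion, delete the words 'purely objective' and the listing of laboratory tests as primary endpoints, and state that assessor masking is partial.

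The cost is a worded form, a chosen scale, a staffing rule and a fixed order of recording at examinations already scheduled. No extra reader or procedure is needed. Masking fails where the endoscopist knows the patient or can see the closed limb from the stoma; the Intervention section puts the closure less than 5 cm away. Recruitment began on 1 January 2016 with endoscopy from 6 months, so examinations already done cannot be masked. The report should therefore say which readings were made under the masked procedure.

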## Trial status

The total enrollment period is presumed to be 3 years, and the patients will be followed up for 5 years. Patient recruitment commenced on 1 January 2016 and the trial is ongoing.

## Data Availability

Data sharing is not applicable to this article as no datasets were generated or analyzed during the current study.

## Abbreviations

BMI: Body mass index
CRF: Case report form
ECOG: Eastern Cooperative Oncology Group
GSRS: Gastrointestinal Symptom Rating Scale
PNI: Prognosis nutritional index
